### Interventions

The study has three arms, two active arms and the control condition ‘treatment as usual’. The active arms added to the control condition ‘treatment as usual’.

### Control condition

Treatment as usual (TAU) comprises regular treatment by the general practitioner, including standard lifestyle recommendations, cardiological and any other health care utilization by the patient. As in Germany all persons have full insurance coverage for medical care including long-term outpatient psychotherapy, TAU represents ‘optimal medical care’.

### Advice in exercise training

The second arm consists of one session of detailed and individualized advice in exercise training (EX). Counselling by an experienced sport medicine specialist is based on the findings of the present spiroergometry and the review of the medical records. The participant receives an exercise-plan with recommendations of endurance exercise time or resistance training based on guidelines for adults from the American College of Sports Medicine and the American Heart Association [22] and individual heart rate range in two different intensities of training for aerobic exercise activity.

### Psychodynamic motivation and training program

The Psychodynamic Motivation and Training program (PMT) follows a psychodynamic stepped care approach. It consists of two to eight sessions of individual psychodynamic psychotherapy in addition to EX. Session frequency, mode (for example. face-to-face consultation, telephone) and dosage are tailored to the individual needs. The maximum dosage is limited to 400 minutes per patient over six months. The individual need is determined by the regular monitoring of physical activity and the patients’ wishes. PMT is conducted by a psychodynamic psychotherapist (board certification or supervision by certified psychotherapist).

PMT is a psychodynamic stepped treatment approach integrating components that have been proven effective for lifestyle change [10] and stress regulation (for example. mindfulness exercises, [23]). The stance of the psychotherapist is actively engaged, goal-directed and directive as described in current manuals of short term psychodynamic psychotherapy [24]. The therapist is willing to teach and guide the patient. The therapist identifies negative transference issues immediately, so that they can be worked through as soon as they arise. Every effort is done to establish the necessary alliance and trust in the therapeutic relationship. As intellectual insight into the need of improved health behavior and the readiness to change are quite separate issues, the therapist must help the patient to experience the benefits of his adaptive wishes and the costs of his maladaptive behavior emotionally. PMT targets the mental and external barriers to improving physical activity by focusing on affects, interpersonal relations and self- and other representations. Unhealthy behavior is considered as the result of maladaptive self-representations (that is, lack of self-care due to blocked positive feelings toward the self) and dysfunctional capacities of anxiety respectively stress regulation (for example, stressful overeating, smoking, addictive television watching, blocked assertiveness to pursue one’s goals). The intervention aims at motivating the patient to be more caring about himself as reflected in improved health behaviors, especially in a physically more active way of living. Physical activity is defined as daily life activities (walking instead of driving, staircase instead of elevator and so on) and home-based exercise training of moderate or vigorous intensity (for example, jogging, swimming, participating in coronary exercise groups, or supervised endurance and weight training).

### Assessment

The assessment includes spiroergometry, blood and urine sampling, measurement of endothelial function and psychometric questionnaires at baseline (T0) and six months follow-up (T1). Spiroergometry, anthropometry and blood sampling are conducted in the Department of Sport Medicine of the University Mainz. Measurement of endothelial function, blood pressure measurement, blood and urine sampling are performed in the Department of Cardiology. Assessors are blinded to the allocation of the patients. Medical diseases and medications are captured by the review of recent medical records and patient interview. Figure 1 gives an overview of the study design and time points of assessment.

**Figure 1 F1:**
[figure not shown]
Study design.

### Spiroergometry

The spiroergometry is performed on a bicycle ergometer according to a standardized protocol. Ergometry is carried out in supine position on a computer-controlled bicycle ergometer (Ergoselect 200P, ergoline GmbH, Bitz, Germany). The ergometry protocol starts at 20, 25 or 50 Watts depending on the expected maximal work load and is increased by 20 or 25 Watts every three minutes. The patients are instructed to keep a pedal rate of 60 rpm. A 12-lead electrocardiograph (ECG) is continuously recorded. Non-invasive blood pressure is measured before exercise, at the beginning and end of every stage, and three and six minutes after exercise. Heart rate is registered continuously by ECG. Oxygen uptake (VO_2_), CO_2_ output (VCO_2_), and minute ventilation (VE), are measured with an open system spirometer (Ergostick, Geratherm Respiratory, Bad Kissingen, Germany). The respiratory parameters are measured breath-by-breath, starting one minute before and ending six minutes after exercise. Breath-by-breath data are averaged over consecutive intervals of three seconds. Patients are advised to cycle until complete exhaustion. Exercising is stopped if one of the following symptoms occurs: chest pain, ST-segment depression, ventricular arrhythmias, systolic blood pressure > 250 mmHg or diastolic blood pressure > 115 mmHg, or a drop in blood pressure.

Lactate is measured at rest and following each workload stage and three and six minutes after exercise by taking capillary blood samples from the hyperemic earlobe. The individual anaerobic threshold (IAT) is determined from the lactate curve by determination of the relative work load (Watt/kg) when a 1 mmol rise in lactate can be found above the minimum lactate equivalent [26,27]. The ventilatory threshold (VT) is determined by analysis of the increase in the respiratory equivalent for oxygen or by decrease in the respiratory equivalent for carbon dioxide [28]. The V-slope method [29] and typical changes in end-tidal gas concentrations (PETO_2_ and PETCO_2_) are examined to search for agreement to control for precision of VT determination.

### Endothelial function

Endothelial function is a valid surrogate marker for cardiovascular disease. The extent of endothelial dysfunction appears to reflect the traditional risk factor burden [30]. The methods employed for the analysis of endothelial function using flow-mediated dilation and constriction (FMD and L-FMC) have been previously published [31]. Briefly, L-FMC and FMD are measured using a Vivid 7 (General Electrics, Munich, Germany) ultrasound platform equipped with a 14 MHz matrix probe and a micrometric probe holder. L-FMC is defined as the constriction observed in the last 30 seconds of a 4.5 minute occlusion of a pneumatic cuff placed distal to the site of arterial diameter measurement and provides information on resting endothelial function. FMD is measured as the maximal dilation observed in the five minutes following deflation of the cuff, that is, during reactive hyperemia, and corresponds to endothelial responsiveness or recruitability. Both markers have been shown to be blunted in the setting of coronary artery disease, hypertension, heart failure, and after smoking [32]. Arterial diameter data are acquired digitally and analyzed in a randomized, blinded fashion using automatic dedicated software whose repeatability and reproducibility has been recently reported [33]. Flows will be analyzed from the digitized audio data using the automated software built in the ultrasound machine.

### Blood pressure measurement

Blood pressure will be assessed by a trained research assistant (blinded to treatment), using the auscultatory method, with a calibrated sphygmomanometer and stethoscope.

### Anthropometry

Anthropometry includes assessment of height and weight, waist-to-hip ratio (WHR) and determination of body composition (body fat, muscle mass, intracellular and extracellular water) by the InBody 3.0 system (Biospace Ltd. 1999) [name]; http://www.e-inbody.com/.

### Blood and urine sampling

Humoral markers will be obtained from fasting blood samples. Serum lipid levels (total cholesterol, triglycerides, and high-density lipoprotein cholesterol), plasma levels of C-reactive protein, fibrinogen, albumin levels and HbA1c are measured immediately after blood withdrawal by routine methods; low-density lipoprotein cholesterol will be calculated by the Friedewald formula. Markers of oxidative and inflammatory stress will be determined in plasma or serum stored immediately after blood withdrawal and centrifugation at −80°C until analysis. The measurements will be done in a blinded fashion in a single batch.

### Psychometric questionnaires

Quality of life is assessed by the EQ-5D™ (EuroQuol Group, Rotterdam, Netherlands) [34]. The EQ-5D™ captures problems pertaining to usual activities and anxiety/depression dimensions, and the respondent’s own assessment of their health status on a visual scale from 0 (worst imaginable health) to 100 (best imaginable health). Coronary artery disease related quality of life is measured with the Seattle Angina Questionnaire (SAQ) [35].

Feelings of vital exhaustion are assessed by the Maastricht Questionnaire [36] and symptoms of fatigue by the MFI Multidimensional Fatigue Inventory (MFI) [37].

Insomnia symptoms were measured by the Jenkins sleep questionnaire [38], covering difficulties initiating and maintaining sleep as well as non-restorative sleep. Occurrence of sleep disturbances is rated for the previous four weeks from: not at all (1), 1 to 3 days (2), 4 to 7 days (3), 8 to 14 days (4), 15 to 21 days (5) to 22 to 28 days (6).

The cognitive and emotional representations of the coronary heart disease are measured by the brief Illness Perception Questionnaire (IPQ) [39]. Changing patients’ illness perceptions may improve outcome in coronary heart disease [40].

Self-rated habitual physical activity was measured by the Habitual Physical Activity Questionnaire [41] and the one item screener from the Heart and Soul Study [17]: ‘Which of the following statements best describes how physically active you have been during the last month, that is, done activities such as 15 to 20 minutes of brisk walking, swimming, general conditioning, or recreational sports?’ Participants chose from one of the following six categories: not at all active, a little active (1 to 2 times per month), fairly active (3 to 4 times per month), quite active (1 to 2 times per week), very active (3 to 4 times per week), or extremely active (≥ 5 times per week). Being ‘not at all’ or ‘a little’ active is considered as physically inactive.

Different dimensions of mental distress are assessed by the Patient Health Questionnaire (PHQ) [42]: depression, anxiety, somatic symptoms and ten common psychosocial stressors. The depression module comprises nine symptoms of depression (PHQ-9). The scores range from 0 to 27. A cut-off ≥ 10 yields a sensitivity of 81% and a specificity of 82% for detecting any depressive disorder [43]. Anxiety is assessed by the Generalized Anxiety Disorder Scale (GAD-7) [44]. Scores range from 0 to 21 with higher values reflecting more anxiety. Somatic symptoms severity is assessed with the 15 items of the PHQ-15. Scores range between 0 to 30. Scores above 15 identify individuals with high levels of somatic symptom severity respectively somatization severity [45]. In addition to symptoms of mental disorders, the PHQ assesses concerns about ten major psychosocial stressors (for example, financial status, family relationships, work, health) on a three-point scale (not bothered, bothered a little, bothered a lot) [42]. For the determination of a subgroup of persons with increased mental or psychosocial distress, the following scores will be calculated: item #3 of the PHQ-9 will be used as a screener for sleep disturbances as a previous study found that the sleep disturbance item correlated strongly with the well-validated Insomnia Severity Index [46]. Sleep disturbances more than half the days will be determined as significant. Clinically significant anxiety will be determined by the two-item version of the GAD-7 [47] with a cut-off score of three or more [48]. The two-item depression module of the Patient Health Questionnaire (PHQ-2) will be calculated also [47]. As in a previous study a PHQ-2 score of two or more predicted the mortality of patients who underwent PCI, we applied this cut-off [49].

### Cognitive functioning

After having started the recruitment for the study we decided to include a computer based version of the Tower of London - Freiburger Version [50] in order to identify changes of cognitive functions. The Tower of London (ToL) is a frequently used neuropsychological test instrument for assessing planning ability in various clinical and healthy populations [51]. In its original version, three balls of different colors are placed on three different rods of different lengths [52] and subjects are presented with a start state and instructed to transform it into a given goal state. In order to solve the problem in the least possible number of moves, subjects are thus requested to plan ahead a solution before manually executing the moves. Three rules have to be followed: (i) only one ball can be moved at a time, (ii) balls must not be placed outside the tower, and (iii) if more than one ball is stacked on a rod, only the topmost ball can be moved.

The ToL problem-set applied in the study consists of an optimized problem selection using eight four-, five-, and six-move problems each of which instantiate a linear increase of problem difficulty [53]. Test duration was limited to a maximum of 20 minutes. The test has been proven responsive to exercise interventions [54,55]. We estimate that 30 complete measurements will be available at study finalization.

### Objectives and hypotheses

The purpose of this study is to examine the effectiveness of the Psychodynamic Motivation and Training program (PMT) for the improvement of physical fitness as determined by the individual anaerobic threshold in patients with stable coronary heart disease as compared to one session of advice in exercise training (EX) only, or treatment as usual (TAU). We have the following hypotheses:

1) PMT is more effective than EX only and TAU concerning change in individual anaerobic threshold.

2) The advantage of PMT will be more pronounced for persons with current mental distress and psychosocial stressors as compared to persons without such stressors.

3) Both active interventions (PMT, EX) are more effective than TAU concerning change in individual anaerobic threshold and secondary endpoints.

4) PMT will be more effective in improving illness perception, quality of life and symptoms of psychosocial distress than EX or TAU.

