### Sample size calculation

As this is the first study on the effectiveness of a psychodynamic motivation and training program, we designed the study primarily to test the feasibility of PMT and possible effects that may be worth following up in a subsequent larger study. The sample size calculation was based on the following considerations: in general, exercise programs for patients with CHD yield increases in the aerobic capacity as determined by the VO_2_-peak of 2.6 ± 1.6 (mean ± standard deviation) versus 0.3 ± 1.4 mL/kg/min in the inactive control groups [61]. This difference corresponds to an effect size of about 1.5 standard deviations. With regard to change of the anaerobic threshold, a recent study on the effects of exercise training in patients with chronic heart failure found at the lactate threshold, a mean workload difference of 43 Watts with a standard deviation of about 17 Watts [60]. For our study we estimated a 50% lower effect size differences, as the exercise training was not supervised and therefore presumably less intensive.

Comparing PMT to EX and to TAU, while controlling the multiple type one error at a level of 0.05, each comparison has to be performed at the nominal level of 0.025 using the Bonferroni correction. With a sample size of n = 30 in each group, a standardized effect size of 0.82 can be detected at the two-sided level 0.025 with a power of 0.80. Assuming that the standard deviation of change in the individual anaerobic threshold is 17 Watts (which is roughly in accordance with results from [60]), this corresponds to an absolute effect of 14 Watts for PMT, which is less than half of the effect reported in [60].

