### Statistical methods

Categorical variables are presented as frequencies and percentages (n,%), continuous variables as means and standard deviations (mean ± standard deviation), or medians and quartiles for variables with skewed distributions (median (25th quartile, 75th quartile). Baseline characteristics of the three treatment groups will be compared with respect to age, sex, socioeconomic status, partnership, cardiovascular risk-factors (for example, smoking, obesity), comorbidity, variables characterizing patients with coronary heart disease (for example, medication) and outcome parameters.

Primary and secondary endpoints will be analyzed according to the intention-to-treat principle. Change from baseline to follow-up will be analyzed by analysis of covariance adjusting for baseline measurement of the respective outcome. Doing so, separate contrast are specified for comparing PMT with EX and TAU, respectively. Cohen‘s effect size will be calculated. In order to determine whether the effect of PMT is modified by presence of significant mental distress and psychosocial stressors at baseline, a test for interaction will be performed. Exposure to significant mental distress and psychosocial stressors will be defined by at least one of the following baseline criteria: PHQ-2 ≥ 2, GAD-2 ≥ 3, sleep disturbances (according to item #3 of the PHQ-9 ≥ ‘more than half the days’), and common psychosocial stressors according to the PHQ module (‘being bothered a lot’ by ‘difficulties with husband/wife, partner/lover or boyfriend/girlfriend’, or ‘stress of taking care of children, parents, or other family members’, or ‘stress at work outside of the home or at school’, or ‘having no one to turn to when you have a problem’). All analyses will be conducted on a two-sided level of significance with *P* < 0.05.

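### Hypothesis 4 and the secondary-endpoint part of hypothesis 3 are directional claims on about 15 unranked endpoints judged at unadjusted two-sided 0.05; they should be labelled exploratory (minor)

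*Protocol article*

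**What the plan says.** Objectives and hypotheses has four numbered hypotheses. The third reads: "Both active interventions (PMT, EX) are more effective than TAU concerning change in individual anaerobic threshold and secondary endpoints". The fourth reads: "PMT will be more effective in improving illness perception, quality of life and symptoms of psychosocial distress than EX or TAU". Neither is marked as exploratory or as subordinate to hypothesis 1.

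Outcomes names one primary variable, the change in power at the individual anaerobic threshold, and then an unordered list of secondary variables. Counting inflammation and oxidative burst as one each, there are 15: VO2-peak, flow-mediated dilatation, HDL, inflammation, oxidative burst, waist-to-hip ratio, BMI, habitual physical activity, EQ-5D visual analogue scale, Seattle Angina Questionnaire, Maastricht Questionnaire, Jenkins questionnaire, and three items of the brief IPQ. Only the Tower of London, which comes on top of these, is described as something to be explored.

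Statistical methods treats both classes of endpoint together: "Primary and secondary endpoints will be analyzed according to the intention-to-treat principle". Both go through the same baseline-adjusted analysis of covariance. The section closes with one rule: "All analyses will be conducted on a two-sided level of significance with *P* < 0.05".

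Sample size calculation has the only multiplicity provision. For PMT against EX and against TAU, "each comparison has to be performed at the nominal level of 0.025 using the Bonferroni correction". The same section and the end of the Background say that the trial is meant mainly to test feasibility and to look for effects that a larger trial could pursue.

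**The concern.** The article recognises multiplicity for two primary contrasts and then states an unadjusted rule for 30 or more secondary tests that bear on numbered hypotheses. It does not say how many endpoints must be positive, or on which contrasts, before hypothesis 3 or 4 counts as supported. Read as it stands, one or two nominally significant secondary results could be presented as bearing out a prespecified hypothesis, even if the primary comparison fails. These results are meant to guide a later trial, so a chance finding could set its direction.

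This is not a detail merely left to an analysis plan that is not shown. The article itself states both the claims and the significance level that applies to them.

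**Working it through.** **1. The plan's own figure.** Inputs from Sample size calculation: n = 30 per group, d = 0.82, two-sided level 0.025, power 0.80, SD 17 W.
- Level: 0.05 / 2 = 0.025 per contrast.
- Noncentrality of the two-sample t-test: d × √(n/2) = 0.82 × √15 = 3.18 on 58 degrees of freedom. Power at two-sided 0.025 is 0.807, against 0.80 stated.
- Absolute effect: 0.82 × 17 = 13.9 W, stated as 14 W.

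The figure reproduces. The two primary contrasts use the whole budget (2 × 0.025 = 0.05), so the stated control does not extend to secondary endpoints.

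**2. Number of tests.**
- Hypothesis 3: 15 endpoints × 2 contrasts (PMT vs TAU, EX vs TAU) = 30.
- Hypothesis 4, minimal set: three IPQ items plus the EQ-5D scale = 4 endpoints × 2 contrasts (PMT vs EX, PMT vs TAU) = 8.

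**3. What counts as a false claim.** Both hypotheses are directional, so only a significant result favouring the more active arm can support them. At two-sided 0.05 that is 0.025 per test when there is no effect.
- Expected false favourable results: 30 × 0.025 = 0.75 for hypothesis 3; 8 × 0.025 = 0.20 for the minimal hypothesis 4 set.
- If all tests were independent, the chance of at least one would be 1 − 0.975^30 = 0.53 and 1 − 0.975^8 = 0.18.

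**4. Allowing for shared arms and correlated endpoints.** Contrasts that share an arm are correlated, and so are endpoints within a patient. The document gives no endpoint correlation; a common value from 0 to 0.7 is assumed. Trials were simulated with three arms of 30, no effect anywhere, and pooled-variance t-tests at two-sided 0.05. Chance of at least one false favourable result:

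| Endpoint correlation | Hypothesis 3, either active arm beats TAU (30 tests) | Hypothesis 3, both arms beat TAU on the same endpoint | Hypothesis 4, minimal set (8 tests) |
|---|---|---|---|
| 0 | 0.50 | 0.07 | 0.17 |
| 0.3 | 0.37 | 0.06 | 0.15 |
| 0.5 | 0.29 | 0.05 | 0.14 |
| 0.7 | 0.21 | 0.03 | 0.11 |

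Repeated runs at correlation 0.5 gave 0.29 to 0.31 for the first column; the differences are simulation error. Widening the hypothesis 4 set to five or seven endpoints gives 0.16 or 0.20 at correlation 0.5.

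**The case against.** The strongest reply is that this is a 90-patient feasibility trial with one primary outcome, and that unadjusted secondary endpoints are common in such trials. Much of that stands.

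- **Status of the claims.** A reader might infer that hypotheses 3 and 4 are confirmatory claims on a par with hypothesis 1. The article never calls them so. The purpose sentence names only the anaerobic threshold, the other variables are called secondary, and the sample size and its error control concern the primary contrasts. What is missing is a label on these hypotheses; the feasibility framing exists, but for the trial as a whole.
- **Likelihood.** A reader might infer that a chance finding in favour of PMT or EX is more likely than not. The figures do not support this. For the 30 tests of hypothesis 3 it reaches one half only with uncorrelated endpoints. Figures of 0.42 to 0.75 arise if significant results in either direction are counted, but a result favouring TAU cannot support hypothesis 3.
- **Literal reading.** Hypothesis 3 speaks of both active interventions. If both must beat TAU on the same endpoint, the risk is small. If PMT must beat both other arms on the same hypothesis 4 endpoint, it is below 0.02. The article does not say that either reading is the decision rule, so the higher figures cannot be excluded.
- **Contrasts.** Statistical methods names only the two PMT contrasts. The EX vs TAU tests counted here come from the wording of hypothesis 3, which needs them.
- **Left to the analysis plan.** How secondary endpoints are ordered could fairly be left there. The level is not left open: the article fixes it for all analyses.

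**Conclusion.** The concern holds in a limited form. Directional effectiveness claims on about 15 unranked secondary endpoints are tied to an unadjusted 0.05 rule, and the only error control stops at the two primary contrasts. Under a global null, a false favourable result somewhere has a chance of about 0.29 for hypothesis 3 (0.21 to 0.50) and about 0.14 for the minimal hypothesis 4 set (0.11 to 0.17). It is 0.03 to 0.07 under the strict reading of hypothesis 3. These figures rest on the count of 15, a common assumed endpoint correlation between 0 and 0.7, 30 analysed patients per arm and no true effect on any endpoint.

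The sample size and the conduct of the trial are unaffected. The issue is what may be concluded from the secondary results, and its severity is minor.

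**What to change.** 1. Under Objectives and hypotheses, label hypothesis 4 and the secondary-endpoint part of hypothesis 3 as exploratory.
2. Under Statistical methods, replace the blanket 0.05 rule. Limit significance claims to the primary outcome for PMT vs EX and PMT vs TAU, each at the two-sided 0.025 level given under Sample size calculation. The 0.025 must be written out: confining the present rule to the primary contrasts without changing its level would leave each at 0.05, in conflict with the sample size section.
3. Report secondary endpoints as effect estimates with 95% confidence intervals and unadjusted P values, described as hypothesis-generating.

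The cost is wording only, with no extra patients or data. The label does not lower any error rate; it changes what may be claimed. The downside is that an isolated secondary result can no longer be called a demonstrated effect, which fits the stated feasibility purpose.
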